## Abstract

**Background:**

Drop out from upper secondary school represents a risk for the future health and wellbeing of young people. Strengthening of psychosocial aspects of the learning environment may be an effective strategy to promote completion of upper secondary school. This paper is a study protocol of a school based cluster randomized controlled trial (RCT) evaluating two school-based interventions, namely the Dream School Program (DSP) and the Mental Health Support Team (MHST). The interventions aim to improve psychosocial learning environments and subsequently school achievements and decrease drop-out and absence.

**Methods/Design:**

The COMPLETE RCT is aimed at youth in upper secondary school, grade 1 (age 15-16 years), and examines the effect of the combination of the DSP and the MHST; and the DSP only, compared with a comparison group on the following primary outcomes: student completion, presence, average grade, and self-reported mental health. Seventeen upper secondary schools from four counties in Norway were randomized to one of the three arms: 1) DSP and MHST; 2) DSP; and 3) comparison (offered DSP intervention in 2018/2019). The study will evaluate the interventions based on information from two cohorts of students (cohort 1 (C1) and cohort 2 (C2)). For C1, data was collected at baseline (August 2016), and at first follow-up seven months later. Second follow-up will be collected 19 months after baseline. For C2, data was collected at baseline (August 2017), and first and second follow-up will be collected similarly to that of C2 seven and 19 months respectively after baseline. Process evaluations based on focus groups, interviews and observation will be conducted twice (first completed spring 2017).

**Discussion:**

The COMPLETE trial is a large study that can provide useful knowledge about what interventions might effectively improve completion of upper secondary school. Its thorough process evaluation will provide critical information about barriers and points of improvement for optimizing intervention implementation. Findings can guide school development in the perspective of improving psychosocial learning environments and subsequent completion of upper secondary schooling.

**Trial registration:**

The trial was retrospectively registered in the ClinicalTrials.gov register on December 22.2017: NCT03382080.

## Background

The value of completing upper secondary schooling is reflected in associations with higher education [1, 2], lower risk of later economic hardship [3], better mental and physical health, and higher life satisfaction among others [4, 5]. Therefore, drop out from upper secondary school represents a risk for the future health and wellbeing of young people [1], as well as societal costs [6–8]. Therefore, it is an explicit aim of authorities in a range of countries, including Norway, to ensure that as many young people as possible complete upper secondary school [6].

The reasons behind any youth’s decision to drop out of upper secondary schooling can be several, intertwined, complex and often have origins in early childhood [9]. Poor mental health is one important cause of upper secondary school drop-out and absence [10–15]. Therefore, special attention to youths’ mental wellbeing and health is needed to promote completion of upper secondary school.

Although conditions outside the school setting interfere with a person’s decision to drop out of upper secondary school, the role and responsibility of schools in striving for each student’s well-being and motivation in school is ubiquitous. Strengthening of psychosocial aspects of the learning environment may be an effective strategy to promote school satisfaction and completion of upper secondary school. The learning environment is the work environment of young people, and a good and inclusive psychosocial learning environment promotes health, wellbeing and learning [16–18].

Poor academic achievement is found to be another strong predictor of school dropout [19]. To stimulate students’ confidence in their own competence and efficacy and thus empower them as learners therefore seems particularly relevant in the school context. A study by Finn and Rock [20] found that academic resilience was partially explained by the extent to which students are actively engaged in school. Engagement in learning activities and in the broader school environment was seen as important antecedents of school achievement. Unlike such characteristics as SES or ethnicity, engagement may be manipulated; that is, educators can encourage engagement behaviors to increase a student’s chances of completing school successfully.

According to Baumeister and Leary [21], one of the central tasks and goals of human life is to sustain a network of close relationships characterized by mutual caring and pleasant, supportive interactions. Enabling a good psychosocial environment in schools through participatory activities stimulates the development of such relationships. In addition, Vinokur and van Ryn [22] concluded that interpersonal conflicts that are expressed in undermining behaviors appear to have a strong concurrent impact on mental health. Building positive and caring relationships in school might prevent negative behavior.

One aspect of the psychosocial learning environment is the teacher-student relationship. A recent systematic review of the role of teacher-student relationships concludes that the teacher-student relationship can play an important part both as risk factor for poor mental health and as a protective factor for good mental health [23]. The review also concludes that positive teacher-student relationships may prevent drop-out and reduce the rate of intention to drop out [23].

Peer relationships and the feeling of connection to peers is another central aspect of the psychosocial learning environment of students. Settertobulte and Gaspar de Matos [24] found that being liked and accepted by peers is crucial to young people’s health development. Those who are not socially integrated are far more likely to exhibit difficulties with their emotional health. Depending on the character of its psychosocial learning environment, the school can be both a risk factor and a protective factor for student’s subjective physical and mental well-being.

Although research exists suggesting positive associations between aspects of the psychosocial school and learning environment and mental health and success in upper secondary school, knowledge about what type of systematic work should be put in place to strengthen these associations is lacking. There is currently a call for targeted interventions to reduce dropout, and robust evaluation designs to measure the effect of these [6]. A meta-analysis of experimental and quasi-experimental studies to reduce dropout from upper secondary school [25], found significant effects of a range of ‘programme types’, indicating the promising role of systematic interventions to come to grips with challenges of dropout. However, the interventions are not described in the meta-analysis which makes knowledge about what elements in these program types work, hard to access. Also, only studies from the US, UK and Canada were included. An important insight from the study is however, the conclusion that implementation quality may be of more importance than what type of programme the intervention is.

A more recent systematic review by Lillejord et al. [6] builds on the review by Wilson et al. [25], and 26 additional studies published between 2010 and 2015. Their analysis concludes that effective interventions are focused on the need of building strong relationships based on confidence between students and teachers, between peers, and between leadership, teachers and other significant actors involved in the work for and with students [6]. Other important factors for successful interventions are ensuring well-established collaborations between involved actors and levels, broad support for the programs, early interventions, and ensuring systematic planning, implementation and evaluation [6].

Despite knowledge about the importance of the psychosocial aspects of the learning environment, the review by Lillejord et al. [6] could not identify any experimental studies with explicit focus on the role of the psychosocial school environment in relation to dropout, and further states that this is a knowledge gap that needs to be filled. A further knowledge gap relates to experimental and quasi-experimental studies on interventions to reduce dropout in a broader array of national and cultural contexts, as the majority of such studies originates from the US and UK [6, 25].

As part of the efforts initiated by the Norwegian Ministry of Education [26] to reduce drop out in upper secondary schooling, a call for research evaluating promising interventions through randomized controlled trials was issued in the spring of 2015. This led to the development of the research project which is described in this study protocol: *COMPLETE – Good psychosocial environments improve the completion of upper secondary school* [27].

The COMPLETE study is an evaluation of the effectiveness of the interventions, and these will be evaluated in a cluster RCT.

### Aims

The aim of the COMPLETE study is to determine the effectiveness of the DPS and MHST among adolescents in upper secondary school with respect to the primary outcomes of completion/drop-out, presence/absence, school grades, and mental health.

Specifically, the COMPLETE study willEvaluate whether the DSP aloneincreases completionincreases presenceimproves school achievementsimproves mental health and wellbeingEvaluate whether the DSP and the MHST combinedincrease completionincrease presenceimprove school achievementsimprove mental health and wellbeing

The COMPLETE study will also evaluate the effect of the DSP and MHST combined and the DSP alone against secondary outcomes of school satisfaction and loneliness.

Furthermore, according to the COMPLETE study program theory (Fig. 1), a range of mechanisms are in place to explain the potential effects of the interventions on the primary and secondary outcomes. These mechanisms are related to psychosocial aspects of the school and class environment, specifically to students’ experiences of relatedness, competence, autonomy, and class climate.

**Fig. 1 Fig1:**
[figure not shown]
COMPLETE study program theory

The aim of the present paper is to describe the study protocol of the COMPLETE RCT.

Finally, the COMPLETE study will through a process evaluation evaluate the implementation quality and fidelity of the DSP and MHST in the intervention schools.

## Methods

### Study design

COMPLETE is an ongoing school-based three-armed cluster RCT in upper secondary schools in four counties in Norway. The trial started in August 2016, and will end in June 2019. It follows two cohorts of students from when they start upper secondary school and until they graduate (C1) or until completion of second grade (C2). The study is non-blinded, and the design includes two intervention groups and a control group. Tables 1 and 2 outline the project data collection and intervention timeline.

**Table 1 Tab1:**
[figure not shown]
COMPLETE trial: Schedule of enrolment, interventions and assessments for Cohort 1 (C1)

**Table 2 Tab2:**
[figure not shown]
COMPLETE trial: Schedule of enrolment, interventions and assessments for Cohort 2 (C2)

### Sample

The size of the sample was based on two prerequisites. First, the implementation of the program in the intervention schools required training of several stakeholder groups. The NGO delivering the universal program set an upper limit to 12 secondary schools which would be manageable for them. Also, in further decisions on sample size, the power calculations with hierarchical structured data [28] followed the procedure applied in a prior comparable psychosocial intervention in Norwegian schools [29]: A hierarchical structure with students in class, a significance level of *p* ≤ .05, power of .80, classes with an average of 20 students, an assumed intraclass correlation of 0.05, and a minimum expected effect size of 0.25 on primary and secondary outcomes (expected effect sizes (Cohens *d*) in similar studies lies between .20 and .50, see meta analyses by Durlak et al. (2011). These power calculations indicated that a sample of 975 students and 49 classes was needed to detect a small effect size of .25.

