#### Process evaluation

The process evaluation builds on two rounds of qualitative interview studies and school visits in 12 schools (the COMPLETE intervention schools) encompassing 19 subdivisions. The studies are conducted in the spring of 2017 (completed) and of 2018. They encompass qualitative interviews, both individual and group interviews, with school leadership (headmaster), subdivision leaders (e.g. study program leaders), class teachers, resource groups for the DSP, student mentors (DSP), students in the DSP, the MHST (counsellors, school nurses, team coordinators) and students in the target group for MHST. Every study (both 2017 and 2018) encompasses approximately 120 interviews and includes around 300 different persons. Every interview has a duration of approximately one hour. Every school visit covers three days and includes both interviews and observation of common areas like the canteen, social zones, outdoor areas, administration area and the teacher common room. Specific interview guides are developed for the different target groups in the study. These are structured interview guides with follow-up questions. The aim of the interviews is to capture the experiences the schools have with the implementation of the two interventions.

All data are stored according to guidelines and requirements for safe storage of data in the University of Bergen storage, SAFE.

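### The stated requirement of 975 students and 49 classes is a two-group, class-level figure; 80% power for 0.25 is not shown for a trial that randomises 17 schools to three arms

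*Protocol article*

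**What the plan says.** The Sample section describes the structure of the calculation as "A hierarchical structure with students in class" and gives the inputs as "power of .80, classes with an average of 20 students, an assumed intraclass correlation of 0.05", a significance level of .05, and "a minimum expected effect size of 0.25 on primary and secondary outcomes". It concludes: "These power calculations indicated that a sample of 975 students and 49 classes was needed to detect a small effect size of .25". It names neither the number of groups nor a school-level ICC.

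The design is described differently elsewhere. The abstract says "Seventeen upper secondary schools from four counties in Norway were randomized to one of the three arms", and that the trial "examines the effect of the combination of the DSP and the MHST; and the DSP only, compared with a comparison group". Randomization of schools confirms that schools were allocated, stratified by county. Process evaluation refers to "12 schools (the COMPLETE intervention schools"), which leaves 17 − 12 = 5 control schools. Recruitment of schools gives 3,003 grade 1 students in cohort 1 (C1) and 3,022 in cohort 2 (C2).

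**The concern.** The calculation departs from the design in two ways. It allows for two groups where the trial has three arms and two comparisons with control. It also stops at the class, one level below the unit that was randomised. Variation between schools is averaged only over the number of schools in a comparison, about 11, and adding students or classes within a school does not reduce it.

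At stake is the only statement in the article about which effects the trial can detect. Set beside 975, about 3,000 students per cohort looks like ample margin for an effect of 0.25. Whether that margin exists depends on a quantity that the calculation leaves out.

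**Working it through.** **1. Reproducing 975 and 49.** Inputs from the Sample section: α = 0.05 (two-sided assumed, since the sides are not stated), power 0.80, d = 0.25, 20 students per class, ICC 0.05.

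- Per group, unclustered: 2(1.96 + 0.8416)²/0.25² = 251.2. This is 252 rounded up, or 250 in round numbers.
- Design effect: 1 + (20 − 1) × 0.05 = 1.95.
- Two groups: 2 × 250 × 1.95 = 975; 975/20 = 48.75, so 49 classes. With 251.2 per group the total is 979.5; with 252 it is 983.
- A one-sided test gives 772 and does not match.

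The arithmetic is sound for one two-group comparison with classes as the independent units.

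**2. Three arms, class clustering only.** 975/3 = 325 per arm, an effective 325/1.95 = 166.7. The standard error of a difference is √(2/166.7) = 0.1095, and 0.25/0.1095 − 1.96 = 0.32, so power is 63% per comparison. For 80%, 3 × 250 × 1.95 = 1,462.5 up to 3 × 252 × 1.95 = 1,474.2 students are needed, or 74 classes. With the 3,003 students of C1 (1,001 per arm), the same formula gives 98%, or 96% with α halved for two comparisons.

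**3. Adding the school level.** The school ICC ρs is not in the article, so it is assumed. The class ICC is ρc = 0.05 − ρs, so that the total stays at the stated 0.05. Schools are taken as equal in size: m = 3,003/17 = 176.6 students (C1) or 6,025/17 = 354.4 (both cohorts). The variance of one school mean is

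v = ρs + ρc/(m/20) + (1 − 0.05)/m,

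and the standard error of a 6 v 5 comparison is √(v/6 + v/5). Power is from the noncentral t on 6 + 5 − 2 = 9 df.

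Example, C1 with ρs = 0.01: v = 0.01 + 0.04/8.83 + 0.95/176.6 = 0.0199; standard error 0.0854; noncentrality 0.25/0.0854 = 2.93; power 74%.

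| School ICC (assumed) | C1: power for 0.25 | C1: detectable d at 80% | C1 + C2: power for 0.25 | C1 + C2: detectable d at 80% |
|---|---|---|---|---|
| 0.005 | 84% | 0.24 | 95% | 0.19 |
| 0.01 | 74% | 0.27 | 85% | 0.23 |
| 0.02 | 58% | 0.32 | 65% | 0.30 |
| 0.05 (extreme bound: no class variance) | 35% | 0.45 | 36% | 0.44 |

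The pooled columns treat the school effect as common to both cohorts. They do not apply to mental wellbeing, which Table 3 lists for C2 only.

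**4. Where 80% is lost.** Power for 0.25 falls below 80% at a school ICC of about 0.007 (t) to 0.012 (normal approximation) for C1, and 0.012 to 0.017 for both cohorts.

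**5. Sensitivity to the split.** The allocation rule with 12 intervention schools permits 6/6/5 or 7/5/5. For C1 at a school ICC of 0.01, power is 69% for 5 v 5 and 78% for 7 v 5.

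**The case against.** The strongest reply is that 975 is a stated requirement, not the size of the trial. One active arm plus control, 11 of 17 schools, holds about 11/17 × 3,003 = 1,943 students per cohort, twice 975. Read as the requirement for a single active-versus-control comparison, a two-group figure even has the right form. This stands: the third arm alone does not take the actual trial below 80%.

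The second reply is that the school-level figures rest on an assumed ICC and an unadjusted test. The article plans mixed models, has a baseline survey and stratifies by county. With 14 df (17 schools minus 3 arms), C1 power at 0.01 is 78% instead of 74%. If baseline also explained 25% of the variance at both levels (an assumption), it would be 88%, and pooled power at 0.02 would be 81%. At 0.05 it stays below 80% either way. This stands too, though consent loss, survey non-response and an adjustment for two comparisons would pull the other way.

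Neither reply supplies what is missing. Extra students shrink the class and student terms of the variance but leave the school term unchanged.

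A reader might infer that the trial is underpowered, or that its tests are invalid. The documents support neither. Power exceeds 80% at the lower end of the assumed range, and Statistical analyses says that the clustering will be adjusted for.

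**Conclusion.** The concern holds in limited form. The figure of 975 students and 49 classes is computed correctly, but for a different design, so as a statement of what this trial needed it is wrong. At that size, power per comparison would be about 63% before any school variance. At the size reached, 80% power for 0.25 is neither established nor refuted: it depends on whether the school ICC lies below roughly 0.007 to 0.012 (C1) or 0.012 to 0.017 (both cohorts). The detectable effect runs from about 0.24 to 0.45 in C1 and 0.19 to 0.44 pooled, the upper ends being extreme bounds. These figures assume equal school sizes, 6 v 5 schools, a total ICC of 0.05, and no allowance for non-response, multiplicity or baseline covariates.

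**What to change.** State in the Sample section that 975/49 is a two-group, class-level figure. Replace it with power and detectable effect for each active-versus-control comparison at the randomised unit, using:

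- 17 schools with the actual split by arm, and the actual student numbers;
- a range of school ICC alongside the class ICC;
- degrees of freedom suited to few clusters;
- any gain from baseline covariates.

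Word the 80% power for 0.25 as conditional on the school ICC. The cost is one recalculation and one rewritten paragraph. No schools need to be added and the design is unchanged; the downside is that the stated power becomes less favourable.

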### Recruitment of schools

Recruitment of schools started in November 2015 with information meetings and written invitations. All upper secondary schools in the four counties were invited to report their interest in participation in the trial. Eligibility criteria were not having been or currently being involved in the DSP or the MHST *or* in similar programs, *or* in other similar research projects. An invitation letter was sent to all schools in the counties via the county administration describing study aims, and project participation. The recruitment process lasted until February 2016. A total of 19 schools reported interest in joining the project, of which 17 schools met the eligibility criteria. These schools comprised approximately 3100 grade 1 students in total. All students are eligible for participation in the DSP and MHST, but for the effect evaluation and survey data collections, students with special needs and students in so called introductory programs (i.e. students with very limited or no knowledge of Norwegian language) were excluded. The final student N is based on students registered at each of the schools the final days before survey data collections. However, it should be noted that due to a high degree of natural fluctuation between schools and study programs the first week of each school year, it is expected that the study N from registries will deviate quite a bit from the survey sample. For C1 the N was 3003 grade 1 students and for C2 the N was 3022 grade 1 students. In C2, approximately 200 class teachers will also receive a survey.

Figure 2 presents the flow chart of participation through the COMPLETE trial per now.

**Fig. 2 Fig2:**
[figure not shown]
Flow chart of participation through the COMPLETE school based randomised controlled trial. N for baseline and follow-up assessments reflect the total number of students participating in each of the assessments, and not the number of participants participating in both assessments

### Randomization of schools

Representatives from Oxford Research who had no prior knowledge of the recruited schools allocated schools to the intervention or control groups according to a computer generated randomization list. To ensure an equal balance of intervention and control groups in each county, stratified randomization was practices in which schools were stratified by county. All schools were given a random number ranging from 0 to 1 by using a randomisation command in the statistics software of Stata 14. Stata generated a random number based on a chosen key. Next, the schools were sorted after the size of the random number in each stratum. The school with the highest number was appointed to the intervention group 1 – I1 (DSP only), the school with the second to highest number was appointed to intervention group 2 – I2 (DSP and MHTS), and the school with the third to highest number was appointed to the control group – C. This procedure was repeated until all schools in each stratum were appointed to a group.

